## 3. Discussion

Globally, in the literature, the application of VR has been considered in many fields, but researchers in Italy have not yet explored the possibility of using it for the widespread exposure of CBT therapy in the work context with the aim of being able to define standardizable and short rehabilitation paths for the improvement of the mental health of workers.

The outcomes of this trial will determine whether CBT rehabilitation can improve the mental health of workers suffering from occupational stress diseases. The secondary outcomes will determine the superiority of VR rehabilitation program with respect to normal exposure therapy.

In summary, the novelty of this study protocol is that, for the first time, a trial explored the efficacy of CBT rehabilitation for Italian workers affected by occupational stress diseases and attempted to determine whether CBT through virtual reality is an advantage to a classical exposure therapy. The work-related stress diseases rehabilitation program described in this protocol has been designed to be amenable to be reproduced and offered to workers. The future application is to offer workers a treatment option with evidence of effectiveness and allow a more rapid reintegration into work.

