What has emerged to date is that work-related stress disorders are the diseases in which occupational factors interact with non-occupational factors and individual conditions [13]. Consistently, in the presence of a worker with anxiety and/or mood symptoms related to work problems, it is necessary to carry out a careful multidisciplinary evaluation of the organization of work, the personal global functioning, and personality traits aimed at recognizing the eventuality of an occupational disease due to work-related stress, such as Adjustment Disorder (AD) or Post Traumatic Stress Disorder (PTSD). The first occurs in response to one or more non-extreme stressors, while the second represents the response that may occurs in people who have experienced or witnessed a life-threatening traumatic event or a catastrophic situation [14,15,16,17].

AD is a frequent diagnosis among workers and is characterized by heterogeneous emotional or behavioral (but also somatic) symptoms, related to traumatic and stressful events, which arise in the three months following one or more work stressful events or organizational conditions. Once the stressor has terminated, the symptoms may resolve within six months (Acute Adjustment Disorder) or may persist for a longer period if the stressor has long-term consequences. Workplace exposure to serious traumatic events can also cause PTSD, a clinical condition characterized by more specific symptoms of re-experiencing, avoidance, hyperarousal, and negative alterations of cognition and mood in relation to traumatic events [18]. 

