### 1.2. Study Hypotheses

Taking into consideration previous literature evidence where metanalyses [26,36] have underlined the greater effect of CBT on occupational stress both on psychological and physiological outcomes than other techniques as relaxation or organizational protocols, we expect a global positive influence of both CBT practices on workers’ mental health outcomes in term of a reduction of mood and anxiety symptoms, as well as a reduction of the physiological stress response (heart rate, respiratory rate, skin conductance, and body temperature) at the end of the whole training (Hypothesis 1). Nevertheless, the single term of the impact is unpredictable because the literature studies are very heterogenous. We hypothesize a greater efficacy from the CBT-VR because the rehabilitation program will be focused on imaginative techniques with gradual desensitization, and it is assumed that VR will allows a better immersive experience. In this regard, we predict greater levels of the physiological parameters during the first session of CBT-VR, as well as greater reduction during the last session with respect to CBT-E (Hypothesis 2). Further, regarding the future application of the method, we believe that work stress disease rehabilitation with CBT-VR could have a better impact in terms of the reduction of workdays lost in line with the improvement of clinical parameters and a better modulation of stress physiological parameters (Hypothesis 2). See Figure 1.

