## 2. Methods

### 2.1. Study Design, Setting, and Timeline

The study is a controlled, randomized, non-profit parallel group superiority clinical trial fulfilling the CONSORT criteria for non-pharmacological treatment. See Figure 2. The estimated time for the entire duration of the study is 13 months as summarized in the Gantt Chart. See Table 1.

A total of 30 patients will be allocated to either CBT-E or CBT-VR. We opted for 15 patients for each group. Based on a sample of 100 healthcare workers of our University Hospital suffering from Adjustment Disorders and treated with CBT at our center (pre-treatment CGI score = 3.95 ± 0.74 and post-treatment CGI score = 2.39 ± 1.07, unpublished data), to point out a difference between the 2 treatment groups (CBT-E and CBT-VR) of at least 1 point at the CGI, the estimated sample size should be at least 26, with 13 patients in the CBT-E group and 13 patients in the CBT-VR group (by considering confidence interval = 95%, statistical power = 90%, ratio of sample size of 1). 

Participants will be assessed at baseline, during each session of CBT, and at the end of the training. Recruitment will be carried out at the outpatient care setting of INAIL, the Italian National Institute for Insurance against Accidents at Work, a public entity safeguarding workers against physical injuries and occupational diseases. The randomized clinical trial will then be conducted at the Center for Work-Related Stress and Occupational Mental Disorders of a major University Hospital in central Italy (Azienda Ospedaliero-Universitaria Pisana, AOUP). The Center includes a multidisciplinary team comprising occupational physicians, psychiatrists, and psychologists. A Trial Management Team (TMT) will be formed to conduct the day-to-day management of the trial. This will include the chief investigator, trial physicians with different roles, and the data manager. The group will meet at least once per week to discuss issues related to the progress of the trial and to ensure the trial is running well.

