### 2.5. Procedures, Outcomes, and Adverse Events

Participants will be randomized with a 1:1 ratio for CBT-E or CBT-VR without any specific criteria in order to prevent any randomization bias. Researchers involved in the outcome measures will be blinded to the allocation. Both the CBT training are assumed to be appropriate and beneficial for participants based on evidence from the literature. The training for each individual subject will begin within 7 days from T0, and each patient will perform 8 sessions of CBT-E/CBT-VR distributed 1 every week. If the subject is unable to perform the session on the scheduled day, a new date will be agreed within one week, failing which the patient would be excluded from the study. The intervention will also be discontinued if the participant withdraws consent or if a change in circumstance results in the participant meeting the trial exclusion criteria and becomes unsafe to engage in the intervention, or if any side effects would arise. These participants will remain in the analysis for data collected up until the date of withdrawal. The intervention is individualized, and progression/modification will be determined through discussions with the subject and the other members of the trial team. Every discontinuation will be replaced in order to reach the trial sample size.

The training protocol of CBT-E/CBT-VR is summarized in Table 5.

All outcomes will be performed before, during, and after the intervention phase, which is 10 weeks in total. The first week involves enrollment, randomization, and baseline data; the second to ninth week involves the training program; and the tenth week involves the patient final report. The outcomes measured will be physiological and clinical parameters, as well as their variations/comparison during the two training programs.

In particular, the physiological signs of stress reporting variations of temperature, skin conductance, heart rate, and respiratory rate will be recorded.

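### The Discussion ranks VR superiority second although the trial is designed and sized for it, and its lead claim that CBT improves mental health rests on uncontrolled pre-post change

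*Protocol article*

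**What the plan says.** Section 2.1 states the design: "The study is a controlled, randomized, non-profit parallel group superiority clinical trial". It also states the arms: "A total of 30 patients will be allocated to either CBT-E or CBT-VR". The only sample size calculation, in the same section, targets a difference of at least 1 CGI point between CBT-E and CBT-VR, at 95% confidence and 90% power, and gives 26 patients (13 per arm). The plan is 15 per arm. Section 2.5 confirms the allocation: "Participants will be randomized with a 1:1 ratio for CBT-E or CBT-VR".

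Section 1.2 sets out two kinds of hypothesis. In Hypothesis 1, "we expect a global positive influence of both CBT practices on workers" refers to improved mood, anxiety and physiological stress response by the end of training. Hypothesis 2 expects CBT-VR to do better than CBT-E.

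Section 3 (Discussion) gives the order of the questions. First: "The outcomes of this trial will determine whether CBT rehabilitation can improve the mental health of workers suffering from occupational stress diseases". Then: "The secondary outcomes will determine the superiority of VR rehabilitation program with respect to normal exposure therapy".

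Section 2.6 lists independent-sample tests and paired tests at p < 0.05 without ranking them.

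**The concern.** Two things are wrong, and they reinforce each other.

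First, the sections disagree on what the trial is for. Randomisation, the superiority label and the sample size all serve the comparison of CBT-VR with CBT-E. The Discussion puts that comparison second.

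Second, the question put in its place is causal, and this design has no control for it. Everyone receives CBT, so the only evidence on whether CBT helps is how patients change from T0 to T1. Part or all of such a change may come from other sources.

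If the Discussion is followed as written, the report could lead with a conclusion that randomisation does not protect and leave the randomised result in second place.

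**Working it through.** **1. Which question was the trial sized for?**

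Inputs from section 2.1: difference 1 CGI point; SDs 0.74 (pre-treatment) and 1.07 (post-treatment); 95% confidence; 90% power; ratio 1. The section does not say which SD was used or whether the test is two-sided; two-sided 5% is assumed here.

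Two-sample t-test with SD 0.74: standardised difference = 1 / 0.74 = 1.35. Solving for 90% power gives 12.6, so 13 per arm and 26 in total. Power at 13 per arm is 91%. The stated figure is reproduced as a between-arm calculation.

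A pre-post question would not lead to 26. The cited series fell by 3.95 − 2.39 = 1.56 points. The SD of change is not given; it depends on the pre-post correlation r:

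SD of change = √(0.74² + 1.07² − 2·r·0.74·1.07)

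- r = 0: √1.6925 = 1.30, which needs 10 patients for 90% power.
- r = 0.7: √(1.6925 − 1.1085) = 0.76, which needs 5 patients.

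**2. Can the design answer the Discussion's lead question?**

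- Arms (sections 2.1 and 2.5): CBT-E and CBT-VR only. There is no waiting-list, untreated or non-CBT arm.
- Evidence left for Hypothesis 1: change from T0 to T1.
- Natural course (section 1.1): AD symptoms may resolve within six months once the stressor has ended, but may last longer if it has long-term consequences. The trial phase is 10 weeks (section 2.5).
- Regression to the mean: patients are recruited at an outpatient service (section 2.1).
- Concurrent care (Table 2): drug therapy that has been stable for at least 12 weeks is allowed.

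None of these can be removed from a T0–T1 change without a comparator.

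**3. Can the size of the problem be stated?**

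With 30 patients pooled, a paired t-test (two-sided 5%, 90% power) detects 0.612 × SD of change:

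- r = 0: 0.612 × 1.30 = 0.80 point.
- r = 0.7: 0.612 × 0.764 = 0.47 point.

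That is 0.80 / 1.56 = 51% down to 0.47 / 1.56 = 30% of the fall in the cited series.

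The chance of a significant paired test if CBT did nothing depends on an assumed spontaneous improvement:

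| Assumed spontaneous change | r = 0 | r = 0.5 |
|---|---|---|
| 0.3 point | 23% | 39% |
| 0.5 point | 53% | 80% |
| 0.8 point | 90% | 99% |

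The answer runs from 23% to 99% with an input that the documents do not give. The table shows only that the risk depends on that input. It is also worked on a CGI score with a pre and a post value, whereas the instrument listed in section 2.3 is the CGI-I, which rates change from baseline and has no T0 score.

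**The case against.** The best case for the plan is that the Discussion is loosely worded and that nothing operative follows from it. It never uses the word primary, no section ranks the analyses, section 1.1 gives both aims side by side, and section 2.6 lists the independent-sample tests first. This stands in part: the documents do not show that the analysis itself makes the randomised comparison a side result. What remains is a conflict between sections 2.1 and 3 that nothing else in the article resolves.

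A second objection is that the rival explanations are limited. The recovery statement in section 1.1 depends on the stressor having ended and concerns AD, not PTSD; participants are workers whose stressor may continue. Table 2 requires a drug-free period or stable therapy and excludes CBT in the previous six months. These points are fair. They narrow the rival explanations but do not replace a comparator.

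A third objection is that both trainings are presumed beneficial from the literature (section 2.5), so Hypothesis 1 is only an expectation. That would be reasonable if the Discussion did not say that this trial will settle the matter.

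A reader might go further and infer that the trial would almost certainly confirm Hypothesis 1 even if CBT did nothing. The documents do not support that, because they give no rate or size of spontaneous improvement. Nor may 0.74 or 1.07 be taken as the SD of change: they are cross-sectional SDs, and the pre-post correlation is unknown.

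**Conclusion.** The point holds as an internal contradiction plus a causal claim without a control. The contradiction is verified: the stated 26 is reproduced as a between-arm calculation (assuming SD 0.74 and a two-sided test), and the Discussion calls that same comparison secondary. The causal limit follows from the two arms alone and needs no numerical assumption.

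Its size cannot be given as a false-confirmation rate, since spontaneous change is not quantified.

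It does not follow that within-arm tests must be dropped. A paired test of change is legitimate as long as it is not read as an effect of CBT.

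**What to change.** 1. State the randomised comparison of CBT-VR with CBT-E at T1 as the primary analysis, in line with section 2.1, and correct the Discussion sentence that assigns VR superiority to the secondary outcomes.
2. Reword the Discussion sentence that says the trial will determine whether CBT improves mental health, and Hypothesis 1 in section 1.2. Suggested sense: change from T0 to T1 will be reported within each arm with a 95% confidence interval as supportive information, and cannot be attributed to CBT without an untreated comparator. The paired tests in section 2.6 may stay.

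Cost: wording only. Arms, patients, visits and data are unchanged. The sponsor gives up a causal claim that the design cannot support.

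Naming the comparison as primary does not settle whether it is adequately powered. With 15 per arm and a 1-point difference, power is about 95% at SD 0.74 but about 70% at the post-treatment SD of 1.07. That is a separate matter.

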## Figures and Tables

**Figure 1 ijerph-20-05735-f001:**
[figure not shown]
Theoretical model of the study protocol.

**Figure 2 ijerph-20-05735-f002:**
[figure not shown]
Study procedures.

**Table 1 ijerph-20-05735-t001:** Gantt Chart.

Gantt Chart	Study Protocol Timeline							
	1–3 m	4–5 m	6–8 m	9–10 m T0 1st w	9–10 m 2–9 w CT	9–10 m T1 10th w	11–12 m	13 m
Protocol finalization								
Ethical and other reg. clearance								
Recruitment of sample for the CT								
CT intervention phase								
data collection								
Data analysis								
Dissemination								

**Table 2 ijerph-20-05735-t002:** Inclusion and exclusion criteria.

*Inclusion criteria*
Diagnosis of AD or PTSD according to the DSM-5 diagnostic criteria
Age ≥18 years
Being a worker
Good understanding of verbal and written Italian
Not having other Axis I diagnoses according to DSM-5 diagnostic criteria
Being drug-free for at least 2 weeks or on stable therapy for at least 12 weeks
Having signed the informed consent to participate in the study
*Exclusion criteria*
Severe cognitive impairment as to compromise the ability to understand the aims and characteristics of the study
Suicidal ideation, neurological, vestibular, or ocular disorders and other clinical entities in the acute phase
Having undergone any CBT training in the 6 months prior to the recruitment

**Table 3 ijerph-20-05735-t003:** Data collected from participants.

Demographic variables (age, gender, education level, civil status, children, family history of mental disorders, personal physical illnesses)
Work variables (field of work, public/private company, big/small company, type of contract, seniority level)
Physiological parameters (hearth rate, respiratory rate, temperature, and skin conductance)
Beck Depression Inventory-II (BDI-II), a 21-item self-report inventory measuring the severity of depression with two subscale (cognitive/affective and somatic) [19]
Self-rating Anxiety Scale (SAS), self-administered, 20-item tool for anxiety symptoms [37]
Job Content Questionnaire (JCQ), a self-administered workplace environment questionnaire to measure social and psychological characteristics of jobs with three main subscales (decision latitude, psychological job demands, and social support [9]
Pittsburgh Sleep Quality Index (PSQI), a self-rated questionnaire that assesses sleep quality and disturbances over a 1-month time interval [38]
Peritraumatic Distress Inventory (PDI), a 13-item self-report questionnaire that measures the level of distress experienced by an individual during and shortly after a traumatic event [39]
Davidson Trauma Scale (DTS), self-rating for measuring the frequency and severity of Post-traumatic Stress Disorder (PTSD) symptoms in three clusters: intrusion/avoidance/hyperarousal [13]
Clinical Global Impressions Improvments (CGI-I), to quantify patient progress/treatment response over time [40]

**Table 4 ijerph-20-05735-t004:** Desktop application elements.

Setting selected in the initial menu
Gender of the character selected in the initial menu
Facial expressions selected in real time by keyboard
Body movements selected in real time by keyboard
Sentences in real time spoken by the operator and listened by the user with a voice that changes tone depending on the gender and personality of the character

**Table 5 ijerph-20-05735-t005:** CBT rehabilitation protocol for occupational stress diseases.

*Session 1*	Global evaluation of the patient. Administration of psychometric instruments. Assessment and engagement, including the development of a problem list and establishment of shared goals. Introduction to the principle of exposure therapy: definition and rationale.
*Session 2*	Classification of work stimuli through a Subjective Units of Distress Scale (SUDS: 0 = no anxiety at all; completely calm; 3 = some anxiety, but manageable: 5 = getting tough; wouldn’t want to have it all the time; 7–8 = severe anxiety that interferes with daily life; 10 = worst anxiety you’ve ever felt). Analysis of some sensations high distressed stimuli/situations avoided. Discussion of catastrophic interpretations. Disadvantages resulting from the avoidance and/or application of other dysfunctional behavioral mechanisms.
*Session 3*	Exposure to a neutral scene aimed at setting the exposition in the VR environment or in the imagination. Inter-session tasks: ABC techniques for work-related emotional stimuli. Practice of relaxing exercises.
*Session 4–8*	Exercises of exposure to the maximum phobic work stimuli, at the maximum level of intensity for an extended amount of time (flooding technique) using the VR environment or in imagination alternating with relaxation exercises. Analysis of the emotions felt during the approach to the phobic stimulus with re-elaboration of it and related thoughts. Identification of dysfunctional behaviors linked to it and identification of more functional behaviors.

## Data Availability

Datasets will be available upon request to authors.
